***Flow Chart for Recruitment***

NFI

Recurrent reactional skin lesions

Informed

Consent

(Form 1)

No

yes

Full Blood Count

Exclude

Hb < 7 gm

TLC < 3000

Platelets < 1 lac

No

Register for trial

(Form 2)

Randomize

Arm 1

Arm 2

Arm 3

Arm 4

Yes

Age < 15 yrs

Wt < 30kgs

Pregnancy

On treatment for TB

H/O Jaundice in last 3 m

Pre-existing bone marrow disease

Hepatic Dysfunction

Known HIV positive

Unable to come regularly

Form E

Yes

Yes

No

NFI < 6 months

Or recurrent reactional skin lesions

Form 3.0

Baseline history

& Examination

Lab tests

Randomised Study Patient

Form 4.0

Baseline ST

Form 5.0

Baseline VMT

Form 6.0

Baseline Lab Investigations

##

Allot 4 weeks treatment box

Follow up Visit

Lab tests

Form 6.1

Clinical

Form 3.1

ST

Form 4.1

VMT

Form 5.1

Serious

Adverse effects

Hb < 7.0

TLC < 3000

Platelet

Count < 1 lakh

Break

Code

Worsening

Improvement

Add steroids

Continue in study

Normal

SGOT < 50

Creatinine < 2.0

Treat accordingly

## Randomization

At the Randomization clinic the MO once again checks to ensure that the patient satisfies both inclusion and absolute exclusion criteria. S/he will fill in the Aza study Registration form(**Form 2**).

If a patient (and parent/guardian where age is less than 18 years) is willing to take part, the MO then obtains an informed written consent **(Form 1)** from the patient (parent/guardian) prior to randomization.

Block randomization will be used to ensure equal recruitment into all the four arms.

The randomization schedule will be developed by an independent unit and the random allocation number will be provided to the medical superintendent at each of the hospitals.

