#### Inclusion Criteria:

Patients with acute (< 6 months) neuritis with or without accompanying type 1 reaction or recurrent reactional skin lesions without neuritis.

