## Enrollment

At enrollment of a patient the MO will collect a randomization number and its corresponding packet that contains the relevant treatment arm for the entire length of the study. The MO will do a detailed clinical examination and fill in **FORM 3.0**

The randomization number will be noted on all the Aza study forms, the patient identity card and the patient medical record, the MO will then arrange for the appropriate lab investigations including the baseline punch biopsy. The MO will fill in the Lab results in **FORM 6.0** and sign the same before issuing the first two weeks blister pack to the patient.

The MO will explain in detail all the precautions (as listed in page 35 of the field manual) to be taken while on treatment in the study, and impress upon the patient the need for regular follow up.

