## Sample size

The sample size calculation was based on the expected improvements in the combined scores (skin, sensory & motor) that the addition of azathioprine to prednisolone would produce. It was calculated that the addition of azathioprine would produce a 25% improvement in the combined scores. This would be a score of 4 allowing for an alpha of 0.05 and beta of 0.80, the minimum sample size is calculated as follows:

n=2x[(Zα +Z1-β)xSD)/ d]2 =2x[(1.96+0.842))x2)/1]2 = 63 per group.

We assumed a ‘lost to follow up’ rate of 15%, and dropout rate due to adverse reactions of 10 %,so minimum of 78 patients would be required per arm, and a total of 312.

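### Block randomisation names no stratification factor, so measurable nerve impairment, which largely decides who can meet the recovery outcome, is left to chance across four arms of 78

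*Protocol*

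**What the plan says.** On allocation, the protocol (Randomization) says that "Block randomization will be used to ensure equal recruitment into all the four arms". The only stated purpose is equal arm size. An independent unit prepares the schedule, and "the random allocation number will be provided to the medical superintendent at each of the hospitals". Neither a stratification factor nor a block size is given, and the text does not say whether each hospital has its own blocks.

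On who enters, the inclusion criterion covers acute neuritis "or recurrent reactional skin lesions without neuritis". The eligibility section also counts as neuritis pain, paraesthesia or tenderness alone, with no measured loss.

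On the outcome, the first primary outcome is a one-point gain in voluntary muscle testing (VMT) and a two-point gain in sensory testing (ST). The Definitions put VMT on a 0-5 scale with impairment at 4 or less.

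On what is known before allocation, patients are identified from skin examination and nerve function assessment in the physiotherapy units, which flag new nerve impairment or recurrent skin lesions. Eligibility refers to VMT and ST findings.

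The pre-planned subgroups are sex, MB/PB and previous/new type 1 reaction. Impairment status is not among them.

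**The concern.** A muscle that is not impaired scores 5 and cannot gain a VMT point. A patient with no measurable impairment is therefore close to a certain non-responder on the first primary outcome, whatever the treatment. Few baseline variables predict an outcome so strongly.

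If one arm happens to receive more such patients, its crude recovery rate falls for a reason unrelated to azathioprine. The fourth objective compares durations of azathioprine, so single arms of 78 are set against each other as well as against control, and the smaller the groups, the larger the chance gaps. Allocation cannot be repaired once patients are randomised. The analysis can then only adjust.

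**Working it through.** **The plan's own figures.** Protocol, Sample size: SD 2, difference 1, 1.96 and 0.842 (the stated beta of 0.80 is evidently power). n = 2 × [(1.96 + 0.842) × 2 / 1]² = 2 × 5.604² = 62.8, so 63 per group, as stated: "2x[(1.96+0.842))x2)/1]2 = 63 per group". The 78 per arm follows from multiplying: 63 × (1 + 0.235) = 77.8, where 0.235 = 1 − 0.85 × 0.90. Also 4 × 78 = 312. Whether that inflation is the right one is a separate matter; 78 is used below because it is the planned arm size.

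**Assumptions.** The share p of patients with no measurable impairment is not in the protocol; 20%, 30% and 40% are used. Such patients are taken to have no chance of recovery. Recovery among impaired patients is taken as 60%; the Background cites 50% in one study and 60% to 70% in others.

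**Chance imbalance.** For two arms of 78, the SD of the difference in unimpaired share is sqrt(2p(1 − p)/78). At p = 0.30 this is sqrt(0.42/78) = 0.073. A gap over 0.10 is 0.10/0.0734 = 1.36 SDs, which has two-sided normal probability 0.17. For all azathioprine patients pooled (234) against control (78), the SD is sqrt(p(1 − p)(1/78 + 1/234)), or 0.060 at p = 0.30. The fourth column comes from 400,000 simulated four-arm allocations and counts gaps of 10 points or more.

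| Unimpaired share (assumed) | SD, two arms | Gap > 10 points, two arms | Gap ≥ 10 points, at least one azathioprine arm v control | Gap > 10 points, pooled v control |
|---|---|---|---|---|
| 20% | 6.4 points | 12% | 30% | 5.6% |
| 30% | 7.3 points | 17% | 41% | 9.5% |
| 40% | 7.8 points | 20% | 47% | 11.8% |

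**Effect on crude recovery.** A 10-point gap moves recovery by 0.10 × 0.60 = 6 points (5 to 7 points for recovery of 50% to 70%).

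**Share of the variance.** At p = 0.30 and no treatment effect, overall recovery is 0.70 × 0.60 = 0.42.

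- Variance of the crude difference: 2 × 0.42 × 0.58/78 = 0.4872/78; SE 7.9 points.
- Part due to imbalance in impairment: 2 × 0.60² × 0.30 × 0.70/78 = 0.1512/78.
- Part left within strata: 2 × 0.70 × 0.60 × 0.40/78 = 0.336/78; SE 6.6 points.

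Impairment status thus carries 0.1512/0.4872 = 31% of the variance of the crude comparison. The same sum gives 0.1152/0.4992 = 23% at p = 0.20 and 0.1728/0.4608 = 38% at p = 0.40.

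**The case against.** The strongest reply is that nothing here is invalid. Unstratified blocks give unbiased comparisons with correct type I error, and the 6-point shift is less than one SE (7.9 points) of the crude difference, which already includes it. That stands. It is also true that adjusting for baseline impairment, or analysing recovery only in impaired patients, would regain most of the lost precision, and that a statistical analysis plan not shown here may provide for either. The primary analysis reads as azathioprine plus prednisolone against prednisolone; if the arms are pooled, gaps over 10 points are rarer, as the last column shows.

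Two stronger readings are tempting.

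- **That the order of procedures prevents balancing.** Under Enrollment, "At enrollment of a patient the MO will collect a randomization number and its corresponding packet" comes before the detailed examination, and the flow chart text lists the baseline ST and VMT forms after "Randomised Study Patient". But the Enrollment section does not mention ST or VMT, the flow chart is available only as text without its arrows, and nerve function is already assessed for flagging and eligibility. The stratum is available; it is simply not used.
- **That allocation is blocked on arm only, ignoring hospital.** The text is silent. Numbers issued at each hospital would fit blocks within hospital.

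Finally, balancing these patients does not answer whether they belong in a recovery analysis at all. That is a question about the outcome and its analysis set, and it remains open.

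**Conclusion.** The point holds as a cheap improvement. The protocol names no stratification factor, although measurable impairment is known at screening and largely decides who can meet the first primary outcome. With 20% to 40% unimpaired, two arms differ by more than 10 points in that share in 12% to 20% of trials, and a 10-point gap is worth about 6 points of crude recovery. The loss is in precision and interpretability; a reader should not infer systematic bias or an inflated type I error.

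The size rests on the assumed unimpaired share, the 60% recovery rate, and no recovery without measurable impairment. The last follows from the scale for VMT. For ST it is a reasonable reading, since the scoring is left to the field manual. Patients who enter with skin lesions alone but have older measurable loss would count as impaired, which is why measured impairment is a better stratum than entry route.

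**What to change.** Have the independent unit prepare block lists within each hospital, stratified by measurable VMT/ST impairment at screening: present or absent. Absent should cover both skin-only patients and those with only pain, paraesthesia or tenderness, so that every patient fits one list. State in the Randomization section that blocks are within hospital, and adjust for the impairment stratum in the recovery analysis. Completing the baseline ST and VMT forms before the number is drawn would be tidy but is optional.

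Cost: up to eight lists (four hospitals × two strata), a matching series of treatment packets for each, and slightly unequal arm totals from incomplete blocks. With blocks of four, for illustration, two arms could differ by at most one patient per list, so at most eight overall. The planned 78 per arm and the treatments do not change. If allocation has already begun, the adjustment alone can still be specified before unblinding.

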## Enrollment

At enrollment of a patient the MO will collect a randomization number and its corresponding packet that contains the relevant treatment arm for the entire length of the study. The MO will do a detailed clinical examination and fill in **FORM 3.0**

The randomization number will be noted on all the Aza study forms, the patient identity card and the patient medical record, the MO will then arrange for the appropriate lab investigations including the baseline punch biopsy. The MO will fill in the Lab results in **FORM 6.0** and sign the same before issuing the first two weeks blister pack to the patient.

The MO will explain in detail all the precautions (as listed in page 35 of the field manual) to be taken while on treatment in the study, and impress upon the patient the need for regular follow up.

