#### Exclusion criteria

- Age less than 15 yrs
- Weight less than 30 kgs
- Confirmed Pregnancy (based on the LMP + Pregcolor strip test)
- Patient on treatment for Tuberculosis.
- Patients with known HIV sero-positivity.
- Patients with Hepatic dysfunction as evidenced by recent history of jaundice and abnormal LFTs on laboratory testing.
- Patients with pre-existing bone marrow dysfunction as evidenced by, abnormal counts, spleenomegaly or on examination.
- Patients with Hypertension (Sustained Diastolic Blood Pressure greater than 90 mm Hg) and Diabetes (Fasting Blood Sugar greater than 110mg/dl or random blood sugar greater than 200 mg/d) are not to be immediately included in the study. However once the condition is brought under control by appropriate medications, they can be included in the study provided they fulfil other criteria.
- Patients unable to comply with monitoring and follow up requirements.
- Patients presenting with Type 2 reactions.

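### The randomisation number and packet are drawn before the liver tests behind one exclusion and before the formal baseline forms, so late-found ineligibility falls after allocation

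*Protocol*

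**What the plan says.** The Enrollment section gives the order in prose. First, when a patient is enrolled, "the MO will collect a randomization number and its corresponding packet", the packet holding treatment for the whole study. Next, "The MO will do a detailed clinical examination and fill in" Form 3.0. The number is then written on the study forms, and "the MO will then arrange for the appropriate lab investigations including the baseline punch biopsy". Results go on Form 6.0, which the medical officer signs before the first two-week blister pack is issued.

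The Patient follow-up procedure section lists the baseline laboratory set: smear indices, blood count, creatinine, AST and ALT.

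The Exclusion criteria include "Patients with Hepatic dysfunction as evidenced by recent history of jaundice and abnormal LFTs on laboratory testing". The Flow Chart for Recruitment instead lists jaundice in the last three months and hepatic dysfunction as two separate items.

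At the randomisation clinic, the medical officer again "checks to ensure that the patient satisfies both inclusion and absolute exclusion criteria" (Randomization section). The only blood test that the flow chart names with cut-offs ahead of registration and randomisation is the full blood count. It prints baseline sensory testing (Form 4.0), baseline voluntary muscle testing (Form 5.0) and baseline laboratory investigations (Form 6.0) after the box "Randomised Study Patient".

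The Statistical analysis section makes the primary analysis intention to treat.

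**The concern.** The protocol asks for all absolute exclusions to be confirmed before randomisation, yet it schedules the liver tests behind one of them after the number has been drawn. The real gate, the signed Form 6.0, is then on the wrong side of allocation. Anyone it stops already holds a number.

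For such a patient there is no clean choice. Removing the patient departs from intention to treat and leaves a gap in a randomisation block. Keeping the patient either places an untreated person in the analysed arm or gives study drug to someone whom the criteria exclude.

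Both primary outcomes are changes in muscle and sensory scores. A patient who leaves after the number is drawn but before Forms 4.0 and 5.0 counts as randomised and has no formal study baseline against which to score either outcome.

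**Working it through.** **Order of steps, side by side**

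| Step | Where stated | Relative to drawing the number |
| --- | --- | --- |
| Nerve assessment at physiotherapy; screening on the pre-treatment form | Identification of eligible patients | before |
| Full blood count with cut-offs | Flow Chart for Recruitment | before, as far as the chart can be read |
| Re-check of inclusion and absolute exclusion criteria | Randomization | before |
| Number and packet collected | Enrollment | the draw itself |
| Examination, Form 3.0 | Enrollment | after |
| Baseline blood tests including AST and ALT, Form 6.0 | Enrollment; Patient follow-up procedure | after |
| Formal baseline ST and VMT, Forms 4.0 and 5.0 | Flow Chart for Recruitment | printed after |
| First blister pack | Enrollment | after the signed Form 6.0 |

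No section places AST, ALT or any other liver test in the first three rows. A site may have a liver result from routine care, but the protocol does not require one. The re-check therefore cannot be relied on to cover the abnormal-LFT element.

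**The plan's own sample size.** Inputs from the Sample size section: SD 2, d = 1, z values 1.96 and 0.842. These refer to a combined score.

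n = 2 × [(1.96 + 0.842) × 2 / 1]² = 62.8, which rounds up to 63 per group, as printed.

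The loss allowance is 15% plus 10%. 63 × 1.25 = 78.75, printed as 78 per arm, and 78 × 4 = 312. It covers loss to follow-up and adverse reactions, with nothing for ineligibility found after allocation.

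**Illustration of size.** The documents give no rate, so let w be an assumed fraction of randomised patients who are affected.

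*Kept, with no treatment effect in them.* The difference shrinks to (1 − w) × d:

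power = Φ[(1 − w) × √(63/2) / 2 − 1.96], where √(63/2) / 2 = 2.806.

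- w = 0: Φ(2.806 − 1.96) = Φ(0.846) = 80.1%
- w = 2% (312 × 0.02 ≈ 6 patients): Φ(2.750 − 1.96) = Φ(0.790) = 78.5%
- w = 5% (312 × 0.05 ≈ 16 patients): Φ(2.666 − 1.96) = Φ(0.706) = 76.0%

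*Removed, on top of the planned 25% loss.* Evaluable per arm = 78 × 0.75 × (1 − w):

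- w = 0: 58.5 per arm, power 77.2%
- w = 2%: 57.3 per arm, power 76.3%
- w = 5%: 55.6 per arm, power 75.0%

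On either route the cost is about 1 to 2 percentage points at 2%, and 2 to 4 points at 5%.

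**The case against.** The strongest reply is that eligibility is checked twice before the number is drawn: once on the pre-treatment form and again at the randomisation clinic. The hepatic criterion also joins a jaundice history *and* abnormal LFTs. On that wording a patient without a jaundice history cannot meet it, and history-taking picks out the candidates beforehand. This largely stands, and it is why the number affected is probably small. It does not remove the point. The flow chart lists hepatic dysfunction separately from jaundice, so the narrow reading is not secure, and under either reading the laboratory element has no scheduled result at the re-check.

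Other objections also stand and limit the point:

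- A reader might infer that bone marrow signs can be found only after randomisation. The documents do not support this: the full blood count and the medical officer's screening come earlier, and nothing says Form 3.0 is the first examination.
- A reader might infer that the nerve tests that decide eligibility follow the draw. They do not: candidates come from patients already having nerve function assessment. Only the formal baseline forms are printed after it.
- A reader might infer that the baseline scores are biased. Blinded measurements taken before the first dose are not affected by treatment, whichever side of the draw they fall on.
- The flow chart is weak evidence. Its layout is not preserved in the text reviewed, and parts of its printed order point the other way: Form 3.0 appears before the randomised-patient box, and several exclusions appear after the randomisation step. The Enrollment prose carries the finding.
- How patients found ineligible after randomisation are treated in the analysis may be set out in a statistical analysis plan that is not at hand. Its absence from the protocol is not part of this point.

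**Conclusion.** The point holds as a matter of sequence. The Enrollment section puts allocation ahead of the baseline blood tests, and the pre-randomisation check of exclusions cannot cover the abnormal-LFT element from any test that the protocol schedules. Patients stopped at Form 6.0, or lost before Forms 4.0 and 5.0, are already in the intention-to-treat set.

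The size is unknown and probably small. The 2% and 5% rates are assumptions with no basis in the documents, and the dilution figures further assume no treatment effect at all in the affected patients.

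A reader might conclude that ineligible patients will certainly enter the analysis, or that the comparison between arms is biased. Neither is supported. The protocol states no rule or rate for such patients. Facts that predate allocation, found before dosing by blinded staff, are not expected to differ by arm. This is an inexpensive improvement that should be made; it does not put the trial's conclusions in doubt.

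**What to change.** In the Enrollment section and the Flow Chart for Recruitment, move collection of the number and packet to after these steps:

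1. the Form 3.0 examination;
2. baseline ST and VMT (Forms 4.0 and 5.0);
3. the blood results, including AST and ALT, on Form 6.0;
4. the medical officer's signature that every exclusion criterion has been checked.

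Leave the baseline punch biopsy after randomisation and before the first dose, so that no one has an invasive procedure for a trial that they do not enter.

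Reconcile the hepatic criterion in the Exclusion criteria with the two separate items in the flow chart. Which wording applies is for the investigators to settle.

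The cost is forms and blood tests for a few patients who are then not randomised. No test is added. Treatment is not delayed, because the first blister pack already waits for the signed Form 6.0.

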## Study interventions

A standardised course of prednisolone starting at 40mg per day and tapered over 2 weekly reducing doses is the accepted practice for treatment of Type 1 reaction under field conditions and in outpatients.4

There are four arms to the study, three interventional arms and one control arm. The four arms of the study are depicted in table 2.

**TABLE 2 :**

|  | 1 | 2 | 3 | 4 | 5 | 6 | 7 | 8 | 9 | 10 | 11 | 12 |
| --- | --- | --- | --- | --- | --- | --- | --- | --- | --- | --- | --- | --- |
|  | Wk  4 | Wk  8 | Wk 12 | Wk 16 | Wk 20 | Wk 24 | Wk 28 | Wk 32 | Wk 36 | Wk 40 | Wk 44 | Wk 48 |
|  |  |  |  |  |  |  |  |  |  |  |  |  |
| Arm 1 | Prednisolone | |  |  |  |  |  |  |  |  |  |  |
|  | | | | | | | | | | | |
| Placebo | | | | | | | | | | | |
| Arm 2 | Prednisolone | |  |  |  |  | | | | | | |
| Azathioprine | | | | | |  | | | | | |
|  |  |  |  |  |  | Placebo | | | | | |
|  | | | | | | | | | | | | |
| Arm 3 | Prednisolone | |  |  |  |  | | | | | | |
| Azathioprine | | | | | | | | |  | | |
|  |  |  |  |  |  |  |  |  | Placebo | | |
|  | | | | | | | | | | | | |
| Arm 4 | Prednisolone | |  |  |  |  | | | | | | |
| Azathioprine | | | | | | | | | | | |

## Patient follow-up procedure

Patients will be followed up from trial entry until the end of the study. Follow up is composed of several elements. A follow up schedule is summarized in the flow chart.

1. At baseline the patient will have laboratory investigations. This will comprise Smear Bacteriological and Morphological Indices (Smear BI and MI); a complete blood count (Hb%, Total Leucocyte Count and Total Platelet Count); Serum Creatinine; Serum AST and ALT.
2. Patients will be followed up fortnightly for the first 8 weeks and then at 4 week intervals with a full blood count and liver function tests done at each visit
3. At each follow up visit a physiotherapist will review the patient nerve function (voluntary muscle test (VMT) and sensory testing (ST) assessment and record the details in specially designed forms. in **FORM 4.1 (**each subsequent visit is indicated as **4.2 to 4.14**) and **FORM** **5.1** to **5.14** (corresponding to the visit number).
4. The PI / study MO will review the patient during follow up visit and evaluate for improvement / worsening of the neuritis. They will record evidence of any primary or secondary end points and compliance with the medication, specifically looking for adverse effects of the drugs. This will be recorded in **FORMs 3.1** to **3.14.**
5. Any participant who has not returned back for a follow up for more than 2 weeks will be contacted at his / her home by phone or personal visit. And attempt will be made to bring them back to the hospital for assessment. A patient who returns to the clinic within 4 weeks of the last visit will be continued in the study and those who do not return within 4 weeks will be removed as dropped out from the study
6. After 20 weeks if a patient wishes to go out of station he/she maybe given 8 weeks of treatment at one point of time and a single follow-up session maybe missed. If two follow-ups are missed concurrently the patient will be treated as per routine clinical practices but will have to be removed from the study.
7. Any patient who has missed their treatment for 4 weeks concurrently will be removed from the study and will be treated as per routine clinical practices.
8. The records of the patients will be flagged in the TLM Patient information systems, to ensure that the study team is informed of any deaths that occur at home. The MO should visit the family to establish the cause of death

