## Patient Follow up: Management of Complications

1. If the neuritis / type 1 reaction worsens (as per defined criteria of VMT and sensory testing) while the steroid is being tapered, then the dose of Prednisolone will be STEPPED UP to the preceding dose. After 20 weeks when Prednisolone has been stopped, if worsening occurs, the patient will be restarted at 40 mg of Prednisolone.
2. If the patient develops medical complications like leucopenia, jaundice or anemia it is imperative that this is investigated as per the protocol to determine the etiology. It should not be assumed that complications are caused by the trial drugs.
3. In case the patient is detected to have potential adverse effects of the drug(s) by lab investigations as listed in the flow diagram, then code will be broken by study coordinator
4. In case the patient develops clinical symptoms and signs suggestive of a severe adverse effect, such as systemic sepsis or gastro intestinal bleed then the patient will be admitted into the corresponding hospital and treated accordingly. The Study Coordinator will be contacted and the case reviewed. The Study coordinator will determine whether to break the code or continue the trial after symptomatic treatment.
5. In case a patient gets pregnant while enrolled in the study, she can be reassured that Azathioprine is highly unlikely to affect the fetus and continued in the study. However she may discontinue if she so wishes, in which case her nerve function assessments will be continued as per schedule.
6. In case of infections such as Tuberculosis, patient will be started on Anti Tuberculosis Treatment (ATT) after relevant investigations and continued in the study.

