## Statistical analysis

The primary analysis will be a comparison of azathioprine plus prednisolone with prednisolone alone for achieving the primary outcome following the “intention to treat” principle. Intention to treat analysis will also be performed for the secondary outcomes.

Analysis of endpoints, comparing time to event in the four arms will be performed.

Pre-planned sub group analysis will be performed for the following subgroups (male, female; MB, PB; previous T1R, new T1R).

A secondary on treatment analysis will be performed to explore the requirement of additional steroids as well as adverse effects with these drugs.

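### Items 5–7 of the follow-up procedure end study participation for missed visits or missed treatment, so obtainable outcomes are lost by rule and the planned intention-to-treat analysis is undermined

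*Protocol*

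**What the plan says.** On analysis, the protocol (Statistical analysis) states: "The primary analysis will be a comparison of azathioprine plus prednisolone with prednisolone alone for achieving the primary outcome following the" intention-to-treat principle. It adds: "Intention to treat analysis will also be performed for the secondary outcomes". A separate, secondary analysis is reserved for patients on treatment: "A secondary on treatment analysis will be performed to explore the requirement of additional steroids", together with adverse effects.

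On follow-up, Patient follow-up procedure opens by saying that patients are followed from entry to the end of the study. Item 2 sets visits "fortnightly for the first 8 weeks and then at 4 week intervals". Three later items end participation early:

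- Item 5 keeps a patient who comes back within four weeks of the last visit; "those who do not return within 4 weeks will be removed as dropped out from the study". Tracing by telephone or home visit is triggered after more than two weeks without return.
- Item 6 says that after week 20 a patient who travels "maybe given 8 weeks of treatment at one point of time and a single follow-up session maybe missed". Two successive missed follow-ups lead to removal and routine care.
- Item 7: "Any patient who has missed their treatment for 4 weeks concurrently will be removed from the study". Routine care follows here too.

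None of these items mentions any further study assessment. By contrast, item 5 of Patient Follow up: Management of Complications, on a pregnant patient who chooses to discontinue, adds "in which case her nerve function assessments will be continued as per schedule".

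**The concern.** Intention to treat needs two things: patients kept in the arm to which they were randomised, and outcomes sought on all of them whatever treatment they took. The Statistical analysis section promises the first. Items 5–7 cut off the second for patients who miss visits or treatment.

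These patients are unlikely to be a random subset. People stop attending or stop taking tablets because they feel ill, feel well or see no benefit, and each reason can depend on the arm and on nerve function. The Background reports adverse effects of azathioprine in up to 15% of patients, so interruption of treatment could differ between the azathioprine arms and placebo. A statistical analysis plan can specify how missing values are handled, but it cannot recover muscle (VMT) and sensory (ST) scores that the protocol stopped collecting.

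The second primary outcome is especially exposed. Recurrence must be present at two tests in a row, so a patient who worsens once and is then removed cannot be counted as a recurrence.

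The timing wording is a separate matter. If item 5's four weeks run from the last attended visit, the rule collides with the visit interval and with the longer absence allowed by item 6, and four sites may apply it differently.

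**Working it through.** **Step 1. Visit schedule.** Item 2 gives weeks 2, 4, 6 and 8 (4 visits), then every 4 weeks. Weeks 12 to 48 give (48 − 12)/4 + 1 = 10 visits. The total is 4 + 10 = 14, which matches the protocol's follow-up forms 3.1 to 3.14. Ten of the 14 visits therefore fall exactly four weeks after the one before.

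**Step 2. Which removals lose an outcome that could have been obtained?**

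| Rule | Trigger | Could the patient be assessed? | Further study assessment provided? |
| --- | --- | --- | --- |
| Item 5 | No return within 4 weeks | Often not; some can be traced | No |
| Item 6 | Two successive missed follow-ups after week 20 | Yes, if back in routine care | No |
| Item 7 | 4 weeks of missed treatment | Yes, may never have missed a visit | No |
| Complications, item 5 | Pregnant patient chooses to stop | Yes | Yes, nerve function on schedule |

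Item 7 is the clearest case. Item 4 has the medical officer record compliance at the follow-up visit, so the lapse may be discovered while the patient is in the clinic and can be tested. The pregnancy rule shows that assessment off treatment was thought feasible. The planned on-treatment analysis only makes sense as a contrast if the primary analysis includes patients off treatment.

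**Step 3. Size.** The protocol does not say how many patients items 5–7 will remove, so a fraction must be assumed. Let m be the fraction of an arm without the outcome and p the recovery proportion among those observed. With no assumption about the missing patients, the proportion in all randomised patients lies between p(1 − m), all missing failing, and p(1 − m) + m, all missing recovering. Taking p = 60% for illustration:

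- m = 5%: 0.60 × 0.95 = 57%, up to 57 + 5 = 62%
- m = 10%: 0.60 × 0.90 = 54%, up to 54 + 10 = 64%
- m = 15%: 0.60 × 0.85 = 51%, up to 51 + 15 = 66%

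For two arms with the same m and an observed difference d, the difference in all randomised patients is (1 − m)d + m(q₁ − q₀), where q₁ and q₀ are the unseen proportions among the missing. As q₁ − q₀ can lie anywhere from −1 to +1, the range is (1 − m)d ± m. These are outer limits, not expected bias. They show how much is left to assumption.

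**Step 4. Item 5's four weeks under two readings.** Take a patient who attends week 20, misses week 24 and returns at week 28, as item 6 permits.

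- *From the last attended visit:* the gap is 28 − 20 = 8 weeks, twice the limit of 4, so item 5 removes a patient whom item 6 keeps. After week 8 the next visit is due 4 weeks after the last, so the grace is 4 − 4 = 0. Tracing, if its two weeks run from the missed visit, starts 4 + 2 = 6 weeks after the last attendance, two weeks after removal.
- *From the last scheduled (missed) visit:* the limit is 24 + 4 = week 28. The patient just complies, and removal under item 5 falls at about the same time as the second missed follow-up in item 6.

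The text does not say which reading is meant.

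**The case against.** A reader might infer that intention to treat has become impossible, or that the trial will be a completers' analysis. The documents do not support this. VMT, ST and endpoints are recorded at every visit until removal, and nothing excludes removed patients from analysis. The definition of recovery fixes no single late time point, and the time-to-event comparison can use patients up to censoring. Handling of missing data may be set out in a statistical analysis plan that is not shown. All of this stands, which is why the analysis is undermined and not ruled out. It does not restore the uncollected scores, and censoring or imputation would have to assume something untestable about them.

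Item 5 is the weakest example. Many patients who stay away despite tracing would be missing under any design. This also stands: the avoidable loss lies mainly in item 7 and part of item 6.

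A reader might also take it as fact that a patient one day late after week 8 is removed, and multiply an assumed lateness rate over ten visits. That needs the strictest reading of item 5, a rate the protocol does not give and independence between visits. It also ignores item 6, which tolerates a missed visit after week 20 and can be read as an exception to item 5. Only the ambiguity is established.

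Finally, the sample-size allowances of 15% lost to follow-up and 10% dropout from adverse reactions should not be charged to these rules. Some losses would happen anyway. For abnormal laboratory values the protocol says to break the code and continue steroids, not to remove the patient. Whether study drug then stops, which could bring item 7 into play, is not stated.

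**Conclusion.** The concern holds in limited form. The protocol commits to intention to treat for primary and secondary outcomes, yet items 5–7 end study assessment for missed visits or treatment, and items 6 and 7 can do so for patients who are still assessable. This undermines the primary comparison, because part of it will rest on missing-data assumptions that the trial cannot check.

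The number affected cannot be derived from the document. Each percentage point of patients without an outcome in both arms leaves one percentage point either way in the difference undetermined by the data. That the loss is related to treatment or outcome is a judgement from the nature of the triggers, not something the protocol states.

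The conflict between items 2, 5 and 6 depends on taking the last visit as the last attended one. On the other reading it largely disappears. The conclusion about lost outcomes does not depend on which reading is right.

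The point deserves correction in the protocol itself, since outcomes not collected cannot be recovered at analysis.

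**What to change.** State in items 5–7 that missing visits or stopping study treatment ends neither outcome assessment nor membership of the randomised analysis set. VMT, ST and skin assessments continue to week 48 for every patient who attends or can be traced and has not withdrawn consent, and all patients are analysed as randomised. Whether study drug continues is a separate clinical decision and should be worded separately.

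Reconcile items 2, 5, 6 and 7 on when the four-week period starts and how it relates to the longer absence allowed after week 20. This review does not choose the rule, because it also governs continuation of treatment and the interval between safety blood tests.

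The cost is a wording change plus some extra tracing, visits and data entry for patients off treatment. For those still attending it should be small, since the hospitals' physiotherapy units already carry out regular nerve function assessment. For non-attenders it means further use of the telephone and home tracing already in item 5, which is real work at four sites.
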